### Sampling

#### Primary Schools

Given the constraints discussed above, a logistically feasible sample size is estimated to be 80 schools. This will be stratified as 30 member, 30 'newly-awarded' (<12 months) and 20 'long term awarded' (≥12 months) schools. A random sample will be drawn from within each strata, however to ensure consistency across the sample and simplify the study design, sampling will be restricted to Government schools (80% of the K-GFYL schools). In addition, for the 'member' group only schools that have recently (< 3 months) joined K-GFYL will be sampled, in an attempt to recruit schools that are not well advanced with the implementation and therefore maximize differences between the groups. With a conservative estimate of intraclass correlation (ICC) of 0.02, and sampling 20-30 students per school (design effect of at most 1.98), for interval behavioral data this sample size will detect a difference of 0.26 based on the example of fruit intake with a mean of 1.99 serves and a standard deviation of 1.14. For data that are categorical, this sample size allows us to detect medium effect sizes, specifically a difference of 10 percentage points between member and awarded services, with 80% power at a significance level of 0.05. Given reasons of cost and concern regarding respondent burden on schools, the sample for the resource use questionnaire will be restricted to 10 schools in each of the three groups.

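### The primary-school design effect of 1.98 does not follow from an ICC of 0.02 with 20 to 30 students per school (1.38 to 1.58), and the 0.26-serve detectable difference appears to inherit it

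*Protocol article*

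**What the plan says.** All the figures are in the protocol article, Methods/Design, Sampling, Primary Schools. Feasibility sets the number of schools: "a logistically feasible sample size is estimated to be 80 schools". The split is "This will be stratified as 30 member, 30 'newly-awarded' (<12 months) and 20 'long term awarded' (≥12 months) schools". The clustering assumption and the design effect stand in one sentence: "With a conservative estimate of intraclass correlation (ICC) of 0.02, and sampling 20-30 students per school (design effect of at most 1.98". It then concludes that "this sample size will detect a difference of 0.26 based on the example of fruit intake with a mean of 1.99 serves", with a standard deviation of 1.14.

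The next sentence, on categorical data, claims a detectable difference of 10 percentage points between member and awarded at 80% power and significance level 0.05. The interval sentence gives no power or significance level of its own and does not say which groups of schools the 0.26 compares. The categorical sentence gives no baseline proportion.

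**The concern.** The parenthesis presents 1.98 as the largest design effect that the two inputs beside it can produce. The usual formula gives a clearly smaller maximum, so one of the three numbers (ICC, students per school, design effect) is wrong or comes from a different calculation.

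This matters because 0.26 serves is the article's only planning figure for interval child-behavior outcomes under the second aim, which compares children in awarded and member-only schools. If 0.26 rests on 1.98, it does not describe the design as stated. A reader weighing a null result would take 0.26 as the smallest difference the study could be expected to see, and could not tell whether the intended ICC was 0.02 or something larger.

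**Working it through.** **Inputs from the Primary Schools paragraph.** ICC 0.02; m = 20 to 30 students per school; 30 member, 30 newly awarded and 20 long-term awarded schools (30 v 50 if the awarded groups are pooled); SD 1.14; 80% power and 0.05, taken from the categorical sentence.

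**Assumptions.** The test is two-sided, and the same power and level apply to the interval sentence.

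**Step 1: design effect.** DE = 1 + (m − 1) × ICC.

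- m = 20: 1 + 19 × 0.02 = 1.38
- m = 25: 1 + 24 × 0.02 = 1.48
- m = 30: 1 + 29 × 0.02 = 1.58
- m = 50: 1 + 49 × 0.02 = 1.98

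At the stated cluster sizes, 1.98 needs an ICC of 0.98/29 = 0.034 (30 students) or 0.98/19 = 0.052 (20 students).

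**Step 2: reproduce 0.26.** Detectable difference = (1.960 + 0.842) × SD × √[DE × (1/n1 + 1/n2)], where 2.8016 × 1.14 = 3.194.

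- 30 v 30 schools, 20 students (600 v 600), DE 1.98: 3.194 × √(1.98 × 2/600) = 3.194 × 0.0812 = 0.259.
- 30 v 20 schools, 25 students (750 v 500), DE 1.98: 3.194 × √[1.98 × (1/750 + 1/500)] = 0.259.

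Both routes combine a sample of 20 or 25 students per school with the design effect for 50 (at ICC 0.02).

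**Step 3: the stated ICC and cluster sizes used consistently.**

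| Schools compared | 20 students, DE 1.38 | 25 students, DE 1.48 | 30 students, DE 1.58 |
|---|---|---|---|
| 30 v 30 | 0.217 | 0.201 | 0.189 |
| 30 v 20 | 0.242 | 0.224 | 0.212 |
| 30 v 50 | 0.194 | 0.180 | 0.169 |

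No cell reaches 0.26. Power to detect 0.26 runs from 85% (30 v 20, 20 students) to 99% (30 v 50, 30 students).

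**Step 4: if 1.98 was the intended value.**

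- *A larger ICC.* With ICC 0.98/29, 1.98 is the correct ceiling at 30 students. At 20 students DE = 1 + 19 × 0.98/29 = 1.64, and 30 v 20 schools (600 v 400) gives 3.194 × √[1.642 × (1/600 + 1/400)] = 0.264, which also rounds to 0.26.
- *Fifty students per school.* 30 v 30 schools (1,500 v 1,500) gives 3.194 × √(1.98 × 2/1500) = 0.164, so 0.26 would not hold.

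**Step 5: the 10-point claim.** The text ties it to member v awarded, so 30 v 50 schools. The check is a two-proportion power calculation on n/DE.

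- 20 students, DE 1.98: 600/1.98 = 303 v 1000/1.98 = 505. Power is 78.7% for 45% v 55%, 79.2% for 50% v 60%, and 89% for 20% v 30%.
- 25 to 30 students, DE 1.98: about 87% or more near 50% prevalence.
- Consistent DE (1.38 to 1.58): at least 91% near 50% prevalence.

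**The case against.** The strongest defense is that 1.98 is worded as an upper limit, and 1.38 to 1.58 do lie below it. That is literally true. It does not explain the number, because the limit that follows from the two stated inputs is 1.58, and 0.26 is larger than those inputs produce for any grouping of the schools.

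A second objection is that 0.26 can be reached in other ways. This stands in part. The 80% power is written only in the categorical sentence. At 90% power, 30 v 20 schools with 25 students and the consistent 1.48 gives 0.260; at 80% power with a level of 0.05/3 the same design gives 0.259. A Poisson standard deviation (√1.99 = 1.41) in place of the stated 1.14 gives 0.262 for 30 v 20 schools with 30 students and 1.58. The article states none of these choices. That 0.26 inherits 1.98 is therefore the likeliest account, not a proven one, and there is no single route to it.

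Third, the consequences are limited. The number of schools was set by feasibility, and the Data Analysis section treats schools as primary sampling units, so neither recruitment nor inference depends on the planning design effect. This stands and keeps the point minor.

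A reader might also infer that the 10-point claim contradicts the 0.26. If the 30 v 30, 20-student, 1.98 basis is carried over, power for 10 points near 50% prevalence is only about 70%. The text does not support that step. It names member v awarded, where power is about 79% even at 1.98 with 20 students. No baseline proportion is stated, and on the 30 v 30 basis 20% v 30% still has 81%. Nor is the lack of a separate figure for the 20-school long-term group a fault, since a condensed article may leave it out.

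**Conclusion.** The design effect is wrong as written: the stated ICC and cluster sizes give 1.38 to 1.58, not 1.98. At 80% power, two-sided 0.05 and SD 1.14, the detectable difference is 0.22 to 0.19 serves (30 v 30), 0.24 to 0.21 (30 v 20) or 0.19 to 0.17 (30 v 50), against the stated 0.26. Two-sided testing, and 80% power for the interval figure, are assumptions.

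The point is minor. If the ICC of 0.02 is right, the error is conservative and the study is more sensitive than stated. A reader might infer that the study is underpowered; on the stated ICC it is not. If instead 1.98 reflects a larger ICC, of about 0.034 to 0.052, then 0.02 was not a conservative choice and the extra sensitivity goes. The article does not show which is the case. The 10-point claim for member v awarded holds to within about one percentage point of power in the least favorable case examined (1.98, 20 students, prevalence near 50%), and comfortably with the consistent design effect.

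**What to change.** Reconcile the three numbers in one of two ways.

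- **If the ICC of 0.02 and 20 to 30 students are right:** replace 1.98 with 1.38 (20 students) to 1.58 (30 students). Restate the detectable difference and name its contrast: 0.22 to 0.19 serves for 30 v 30 schools, 0.24 to 0.21 for 30 v 20, or 0.19 to 0.17 for member v all awarded.
- **If 1.98 was intended:** correct the ICC or the cluster size that produces it, and name the contrast and number of students per school for which 0.26 holds.

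Either way, state the power and sidedness for the interval figure. The 10-point figure can stay for member v awarded; adding the baseline proportion it assumes would make it checkable. The cost is rewording one paragraph. No extra schools or students are needed.

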#### Preschools and early childhood settings

Given the time and funding constraints a logistically feasible sample size is deemed to be 50 preschools and services; stratified as 20 member and 30 awarded for preschools and the LDC services. For continuous data, this sample size will detect a difference of 1.0 unit for a variable such as staff ratings of support for health promotion activities, with a mean of 8.4 and a standard deviation of 1.3, with 80% power and significance level of 0.05. For data that are categorical, this sample size provides the ability to detect large effect sizes, specifically a difference of 40 percentage points between member and awarded services, with 80% power at a significance level of 0.05. At the time of planning, thirty FDC services are members and awarded in the K-GFYL program and each of these services will be invited to participate in the evaluation.

A set of open-ended questions will be given to preschool parents (from 5-7 participating kindergartens) to examine their experiences with the K-GFYL intervention. This sample will be purposively drawn from the participating kindergartens to include member and awarded kindergartens from socio-economically disadvantaged areas and where possible, from at least one area with a high culturally and linguistically diverse population.

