### Data Analysis

Data collected will be entered into Stata 10.1 for cleaning and analysis. Preschool, primary school and LDC environmental data that is categorical in nature will be analyzed using Chi-squared or Fisher's exact tests depending on sample size. Data that is continuous or interval in nature (eg staff ratings, frequency of actions etc) will be analyzed using t-tests if normally distributed or by the Kruskal-Wallis equality-of-populations rank test if non-normally distributed. Analysis of the child behavioral data will be at the school level (school as the Primary Sampling Units, PSUs, using the *svy *commands in Stata) using logistic regression (binary and ordinal), and generalized linear models regression with a Poisson distribution for interval data. Child behavioral data will be adjusted for child age, gender and maternal education (as an indicator of socio-economic status). Analysis of the FDC data will be at the local government area level (as the PSUs). Continuous or interval impact and outcome data will be compared using the Wald test of difference in group means, and data that is categorical or ordinal will be analyzed using logistic regression and the design corrected chi squared statistic. An inductive thematic analysis will be conducted for qualitative data.

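### The preschool and long day care sample (20 member v 30 awarded) gives about 74% power for a 1.0-unit difference with SD 1.3, not the stated 80%

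*Protocol article*

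**What the plan says.** In the protocol article, under Sampling, the subsection on preschools and early childhood settings sets a feasible sample of 50, "stratified as 20 member and 30 awarded for preschools and the LDC services". On continuous outcomes it then claims that "this sample size will detect a difference of 1.0 unit for a variable such as staff ratings of support for health promotion activities". The planning values behind this claim are a mean rating of 8.4 and an SD of 1.3, and the operating characteristics are given as "with 80% power and significance level of 0.05". The subsection does not say whether the test is one- or two-sided, and it mentions no allowance for non-response or other adjustment in this calculation.

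Under Data Analysis, continuous environmental data from preschools, primary schools and LDC services "will be analyzed using t-tests if normally distributed or by the Kruskal-Wallis equality-of-populations rank test if non-normally distributed". No clustering correction is described for the preschool and LDC environmental data, so the service is the unit of analysis and the calculation is an ordinary two-sample comparison.

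**The concern.** The sentence gives everything needed to recompute the power: both group sizes, the difference, the SD, the significance level and, through Data Analysis, the test. A quick check shows that the standard error is too large for a 1.0-unit difference to be detected with 80% power. The article therefore contradicts its own inputs. This is not a detail left to an unseen analysis plan, because no analysis plan can change what 20 v 30 with SD 1.3 delivers.

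The first aim compares environments in awarded and member-only settings, and this is the only power statement for continuous data in preschools and LDC services. Anyone who weighs a non-significant difference in staff ratings against it would take the chance of missing a true 1.0-unit difference to be 20%, when it is about 26%.

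**Working it through.** **Inputs.** From the sampling subsection: n₁ = 20 member, n₂ = 30 awarded, difference d = 1.0, SD = 1.3, significance level 0.05, stated power 80%. From Data Analysis: two-sample t-test. Assumed: two-sided.

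**1. Standard error of the difference.**
SE = 1.3 × √(1/20 + 1/30) = 1.3 × 0.2887 = 0.3753.
Standardised difference = 1.0 / 0.3753 = 2.665.

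**2. Attempt to reproduce the stated 80%.**
- Normal approximation: Φ(2.665 − 1.960) = Φ(0.705) = 0.760.
- Planned t-test: noncentral t with 20 + 30 − 2 = 48 df, noncentrality 2.665 and critical value 2.011 gives 0.743.

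Neither gives 80%. Type II error by the t-test is 1 − 0.743 = 0.257.

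**3. Difference detectable with 80% power.**
- Normal approximation: (1.960 + 0.842) × 0.3753 = 1.051.
- t-test, solved numerically: 1.073.

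Both print as 1.1 to one decimal.

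**4. Sample needed for 1.0 unit at 80%, keeping about 2:3.**
By the t-test, 23 v 34 gives 79.9% and 23 v 35 gives 80.4%. This only measures the size of the gap; it is not a proposal to recruit more services.

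**5. Other ways the 80% might have been obtained.**

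| Variant (d = 1.0, SD = 1.3) | t-test | Normal approx. |
|---|---|---|
| 20 v 30, two-sided | 74.3% | 76.0% |
| 25 v 25, two-sided | 76.0% | 77.6% |
| 20 v 30, one-sided 0.05 | 83.7% | 84.6% |
| 40 v 60 (both settings pooled, 20 v 30 in each), two-sided | 96.2% | 96.5% |

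None comes within 2 percentage points of 80%.

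**6. Rounding.** The difference and the SD are each printed to one decimal.
- d = 1.0, SD = 1.25: 77.5% (t), 79.1% (normal).
- d = 1.049, SD = 1.3: 78.2% (t), 79.8% (normal).
- d = 1.049, SD = 1.25: 81.3% (t), 82.8% (normal).

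Unrounded inputs that give 80% and print as 1.0 and 1.3 therefore exist.

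**7. Check on sidedness.** The same subsection also claims 80% power for a 40-percentage-point difference in categorical data. The article gives no base rates. With 20 v 30 and 30% v 70% as an assumed pair, uncorrected power is 81% two-sided and 89% one-sided. That companion figure fits a two-sided calculation better.

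**The case against.** The best defence is rounding. By the normal approximation with SD 1.25, the difference detectable with 80% power is 1.01; by the t-test it is 1.03. Both print as 1.0, and the SD prints as 1.3. The sentence may therefore be a correctly rounded report of a sound calculation. That stands as an explanation of origin and is a reason not to call it a blunder. It does not make the sentence right as printed: at exactly 1.0 unit, power stays below 80% by either method even with SD 1.25.

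Sidedness is not stated, and a one-sided test would give about 84%. Two-sided is thus an assumption here, but nothing in the article points to one-sided testing, and 84% is not the stated figure either.

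It is also fair that the sample was fixed by feasibility and that the staff rating is offered only as an example. The sentence did not determine the sample size.

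A reader might infer two stronger criticisms, and neither holds.
- **That the rank test would lower power further.** The familiar relative efficiency of 0.955 applies to normal data, whereas the plan uses the rank test only for non-normal data. In simulations of 20 v 30 with SD 1.3 and a 1.0-unit shift, its power was about 84% for Laplace data and about 93% for skewed exponential data. These shapes are assumptions, but they are enough to defeat a general claim of lower power.
- **That the 50 services are divided evenly between preschools and LDC services, with much lower power in each.** The wording leaves open whether 20 and 30 are counts per setting or in total, but no section states an even division. Power figures built on one are conjecture.

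**Conclusion.** The stated 80% does not follow from the printed inputs. With 20 v 30 services, SD 1.3 and a two-sided 0.05 level, power at 1.0 unit is about 74% by the planned t-test (76% by the normal approximation). The 80%-power detectable difference is about 1.07 (1.05). The shortfall is about 6 percentage points of power, or 0.05 to 0.07 units on a rating with a mean of 8.4. It may come from rounding.

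The conclusion rests on reading the printed values as exact, on a two-sided test and on the service as the unit of analysis. It does not show that the design is unsound or that more services are needed. It holds if 20 v 30 is the sample in each separately analysed setting, and also if it is the total analysed together. Because the article does not say which is meant, that point needs clarifying.

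**What to change.** Restate the continuous-data sentence to say that the sample will detect *a difference of about 1.1 units with 80% power (1.0 unit with about 74% power), two-sided significance level 0.05*. If unrounded inputs were used, print them so that the figure can be reproduced. In the same place, say whether the 20 member and 30 awarded services are the sample for each of preschools and LDC, or the total for both.

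The cost is a wording change and a slightly less favourable figure. Recruitment targets, instruments and tests stay as they are.

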### Data Collection Instruments

The *School Environment Questionnaire (SEQ) *is a 129 question instrument designed to examine key elements of the school environment. The questionnaire contains items that have been used previously in similar studies we have conducted [17-19] and forms the structure for key informant interviews to capture physical (eg. adequacy of sporting and active play equipment), policy (eg. adoption of nutrition and physical activity policies) and socio-cultural (eg. teachers' role modeling physically active behaviors) elements of the school environment. This structured interview is conducted with 2-3 members of the school staff and also captures information related to the following areas: general demographic information; the food service; school food/nutrition policy(ies); the nutrition environment; school physical activity policy(ies); the physical activity environment; staff knowledge, skills and attitudes; and program implementation activities. Interviews will be completed in a single session approximately 45 minutes in duration and will be conducted by trained research staff. For each question one response will be recorded and where there is disagreement, staff will be asked to discuss the issue until consensus is reached.

The *Child Health Questionnaire *contains 51 items and is designed to capture information from parents/carers of primary school children regarding their child's physical activity, sedentary and nutrition related behaviors. The majority of survey items have previously been used by our research group in similar studies [3,8,17,19,20]

The *Economic Resource Questionnaire *is designed to determine what resources the school has used to implement activities for the K-GFYL intervention. It is to be completed by the staff member who has the most knowledge about these activities and in most cases, this will be the same staff member(s) who complete the SEQ (above). The specific activities reported on will be extracted from the SEQ and will reflect school activities undertaken in the previous three school months. For each activity, the following details are required: a brief description of the activity, frequency of activity, target group (eg. whole of school or a particular class), the category of costs (personnel time, equipment, food and drink, other resources), quantity, provider of the resource (school, parents, external sponsor, grant etc), and the actual cost (if known). This questionnaire is for use in primary schools only and the data will be collected either through a face-to-face or telephone interview.

The *environmental questionnaires *used in the preschool and early childhood settings are similar to the SEQ and have been used previously by our research group for similar studies [17]. Whilst the questionnaire is consistent across settings, it is adapted to the nature of each of the services (FDC, LDC and preschool) to be examined. The questionnaire comprises 12 sections, containing approximately 244 items in total and captures the following: general demographics; food service; children's daily activities; staff knowledge; skills and attitudes; communication strategies; physical environment; policy environment; and intervention activities.

A child *lunch box survey *will also be conducted in preschools and the FDC services. These settings were chosen as children bring lunch and snacks with them each day in both settings and because of previous use of the survey in these settings. The survey is observational and designed for use by the teacher/carer who records the number of children bringing items from a range of food/drink groups for lunch, snack or both (incidence reporting). The food groupings are: fresh fruit and vegetables; packaged snack foods; high fat/high sugar snack foods; healthy snacks; sandwiches/rolls with high sugar filling; sandwiches/rolls with healthy fillings; and chocolates/sweets/lollies. The drink categories are: water, sweet drinks, plain milk, other.

#### Policy analysis

Two policy checklists were developed for this evaluation based on our existing knowledge of school and service nutrition and physical activity policies and current evidence about important policy elements to promote nutrition and physical activity in children's settings [21-23]. The checklists have been piloted with a random sample of schools and services to ensure they extract the information required consistently across policies. After some refinement of wording, these checklists have been finalized (below) and will be used by trained research staff to determine the elements contained in the nutrition and physical activity policies. Research staff will also provide a rating (very poor, poor, good, very good) of 1) the structure and layout; and 2) readability and ease of understanding (simple and clear) of each policy.

Policy elements for nutrition/food-related policies:

1. Limit or restrict foods and drinks available through the food service (internal/external)

2. Ensure the food service menu meets government guidelines for healthy eating or nutritional quality

3. Ensure the availability of water for students/children

4. Restricting students' access to stores and food outlets, schools only

5. Restricting vending machines on the premises, schools only

6. Restricting foods associated with fundraising

7. Restricting foods associated with special events (e.g. birthdays, functions)

8. Setting aside adequate time for children to eat lunch/snacks

9. Promoting or restricting the types of foods that may be brought from home

10. Teaching that is focused on food and nutrition in the curriculum

11. Distribution of information to parents about healthy food and eating

12. Staff acting as role models in the area of healthy eating

13. Encouraging children to adopt healthy eating behaviors

14. Operating the food service on a not-for-profit basis

15. Foods are not used as rewards or punishment

16. Designated fruit/vegetable breaks

17. Promoting children's participation in growing, preparing and/or cooking food

18. Importance of healthy eating on learning outcomes (eg reduced absences, better behavior), schools only

19. Engaging with allied health professionals to implement health promotion activities

20. Providing professional development for staff regarding healthy eating

Policy elements for physical activity-related policies:

1. Providing access to play equipment out of class/session time

2. Promoting active transport to and from school/service

3. Planned teaching focused on active play

4. Providing information to parents about children's physical activity/active play

5. Promote active play/physical activity outside of service/school

6. Planned activities during school/session times

7. Promote a positive attitude toward active play and physical activity

8. Offer challenging and varied physical activities for children

9. Description of resources available for students to engage in physical activity (e.g. equipment, challenges, excursions)

10. Providing professional development for staff related to active play/physical activity

11. Ensuring that all children are active most of the time during physical activity sessions

12. Active play/physical activity is inclusive of all children, no matter ability or level

13. Ensuring children have access to water during active play and at all times

14. Encouraging participation in sport and physical education

15. Planned break time (e.g recess, lunchtime) physical activities

16. Ensuring the time allocated for formal physical education is consistent with recommended or mandated physical education times

*Open-ended question *data will be collected from kindergarten parents to explore their awareness of healthy eating and physical activity kindergarten activities; the challenges parents face around healthy eating and physical activity for their child and family; and additional comments on their child and family eating and physical activity habits.

